## Materials and Equipment

### Overview

NeuroAD is a factorial, placebo-controlled, double-blind and randomized clinical trial in which 100 patients at the mild stage of AD are randomly assigned to four groups: 1—active tDCS and active cognitive intervention; 2—sham tDCS and active cognitive intervention; 3—active tDCS and placebo cognitive intervention; and 4—sham tDCS and placebo cognitive intervention. All of the patients will be subjected to tDCS and cognitive intervention applied for 24 workdays. At the end of the trial, patients who received active tDCS and achieved clinical response will be invited to maintain tDCS bimonthly for 12 months, as part of a long-term study of tDCS for AD; those who did receive sham tDCS and did not respond will be offered 24 open-label daily sessions of tDCS (crossover study); finally, those who showed response with cognitive intervention (real or placebo) and sham tDCS will be referred to other neuropsychological centers specialized in treating dementias in our Institution.

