### Randomization and Blinding

The participants will be randomized into 1:1:1:1 blocks using the random number generator of an open-access randomization software program^1^. This sequence will be remotely performed by a blind researcher not involved in other research procedures. After the randomization process, a blinded staff member will perform patient allocation between the groups. Hidden allocation will be performed with closed, sealed and sequentially numbered envelopes. The participants will be identified by codes and will also be blinded; that is, they will ignore the arm of the study to which they will be allocated. The evaluation and treatment will be performed by independent researchers, who will identify the patients by their respective codes and will be blinded to the other research procedures. Data analysis will be performed by a professional not involved in any stage of patient recruitment, screening, assessment, or intervention. The effectiveness of the masking will be assessed after completing the treatment by interviewing the raters, who will be asked what type of treatment (active or placebo) they believe that the patient received. The relatives of participants will also be blinded and asked, at the end of the treatment, to which group they believe that the patient was allocated. The patients will also be asked questioned about which group they believe have been allocated. We decided to assess the effectiveness of the blinding by asking the relatives and/or caregivers of the patients because the patients have mild AD.

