#### Proposed Analysis

Intent-to-treat analysis will be used; that is, all participants will be included in the analysis, including those who drop out before completing the treatment. However, high or different rates of dropouts between the treatment arms may lead to biases. Thus, a sensitivity analysis will be performed with different assignment procedures to assess the value of the data. The best strategy resulting from the following methods will be chosen: last observation carried forward, complete case analysis, likelihood-based methods, or multiple imputation.

Descriptive statistics will be used to describe clinical and sociodemographic characteristics and the primarily and secondary outcomes of each group at the baseline. The groups will be compared by analysis of variance (ANOVA), for continuous variables, or the chi-square test, for categorical variables.

The primary outcome will be examined by split-plot ANOVA with one dependent variable (ADAS-Cog score) and two independent variables, namely, one intra-group variable and one inter-group variable. The within-subject variable will include time (baseline, post-treatment and 12-month follow-up), and the effects of the treatment condition (active or placebo tDCS; active or placebo cognitive intervention) will be examined as a between-groups variable. *Post hoc* comparisons using Bonferroni correction will be performed where appropriate. Finally, the effect sizes regarding inter-group comparisons will be calculated using the eta squared (*η*^2^), and effect sizes regarding intra-group comparisons will be calculated by means of Cohen’s d using Hedges’ correction (Fritz et al., 2012), adopting the significance level of *p* < 0.05. For all variables of the secondary outcomes, the same analysis strategy will be used. Non-parametric tests will be performed if some of the outcomes do not meet the conditions necessary for parametric analysis.

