Considering the different evaluations with the same cognitive tests throughout the clinical trial, the improvement in the performance of these tests may result from practice and not from the intervention applied (Chelune, 2010; Goldberg et al., 2015). A RCI will be used; it serves to assess whether the changes identified comparing pre- and post-intervention data can be attributed to the procedures used or are mere oscillations, artifacts, or measurement errors (Jacobson and Truax, 1991) resulting from repeated practice effects (Chelune et al., 1993). The RCI, correcting for practice effects and using the Iverson’s standard error of the difference will be calculated based on the Duff’s (2012) formulae.

The follow-up analysis will calculate the primary outcome (i.e., a decline in cognitive state). As proposed in Phase 1, the same cutoff will be used to classify clinical improvement (3.76 points in the mean, with an SD of 1.33 points in the ADAS-cog). The primary outcome measure will be calculated considering the differences between clinical improvement and clinical relapse (or censored if relapse did not occur). Kaplan-Meier survival analysis will be used to calculate this outcome. To investigate interactions of risk factors, the following variables will be observed: demographics characteristics (age, gender, level of education), clinical condition (duration of illness, comorbidities and neuropsychiatric states) and “methodological” variables (Phase 1 group and crossover). The hazard ratio will be estimated using the Cox proportional hazards (to each predictor variable or covariate)”

Regarding safety, adverse effects will be analyzed in terms of the ratio in each group and period (before and after treatment) and analyzed using Fisher’s exact test. Multivariate regression will be used to identify predictors of response. The outcome variables will be tDCS and cognitive intervention, and the predictors will be age, gender, comorbidities and use of medication.

The effectiveness of the blinding will be analyzed by using the chi-square test, comparing the ratio between errors and correct responses. Furthermore, these tests will be compared between patients with clinical response and those who failed to improve.

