**Figure 2 F2:**
[figure not shown]
Flowchart of phases I (double-blind factorial clinical trial), II (crossover) and III (follow-up) of the Neurostimulation combined with Cognitive Intervention in Alzheimer’s disease (AD) Study (NeuroAD). T0: Baseline, pre-intervention measurement. T1–T8: intervention, tDCS and cognitive treatment. T9: endpoint, post-intervention measurement.

The phase I is a double-blind, randomized, factorial clinical trial in which tDCS will be applied in parallel to cognitive intervention in AD patients. This stage includes two measurement time points: baseline (week 0) and post-treatment (week 8). The data collection sessions will be performed by treatment-blinded investigators including the primary and secondary outcomes assessments. The pre-measurement consists of a screening and measurement part. The screening part contains data of the DSM-IV-TR, NINCDS-ADRDA criteria, CDR, MMSE and health questionnaire (including questions about disease duration, comorbidities and use of medication). Adverse effects will be assessed at each session, wherein the tDCS rater will ask the patients whether they feel any discomfort or pain and whether this could be related to tDCS.

Phase II is an open-label, crossover phase in which non-responders from groups (2) and (4) (i.e., those receiving sham tDCS) receive a course of active tDCS using the same parameters and montage of phase I, that is, a direct current of 2 mA (current density = 0.13 mA/cm^2^) for 30 min/day for 24 days, in respective six brain regions.

Phase III is the longitudinal study of NeuroAD in which all active-tDCS responders—that is, responders from groups (1) and (3) from phase I and responders from phase II will be enrolled in a bi-monthly 1-year follow-up. Thus, two months after the last session, the participants will receive ten consecutive tDCS sessions (from Monday to Friday), which will be repeated every other month, until completing a one-year period (totaling 70 follow-up sessions). The tDCS parameters will be the same as those applied during the period between baseline and post-treatment, and the same cortical areas will be stimulated.

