The expected significant improvement is reaching 3.76 points in the mean ADAS-Cog, with a SD of 1.32 points, according to Rabey et al. (2013). Thus, we consider the difference of at least three points in the ADAS-Cog and in the pre- and post-treatment measures to be clinical improvement. All participants with clinical improvement will be considered as respondents.

In all steps, the primary and secondary outcomes assessments will be repeated. The pre-intervention measurement is planned to be performed in the week before the intervention starts and the post-intervention measurement is planned for the first week after the intervention.

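### The regression meant to find predictors of response names the two randomised treatments as its outcomes and contains no response measure, so as written it only checks baseline balance

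*Protocol article*

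**What the plan says.** All references are to the protocol article.

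- **Aim** (Proposed Analysis, in the paragraph that begins with safety): "Multivariate regression will be used to identify predictors of response".
- **Model** (the next sentence): "The outcome variables will be tDCS and cognitive intervention, and the predictors will be age, gender, comorbidities and use of medication".
- **Status of the two named outcomes.** The Overview defines the randomised groups by them: "1—active tDCS and active cognitive intervention; 2—sham tDCS and active cognitive intervention; 3—active tDCS and placebo cognitive intervention", and a fourth group with both treatments inactive. Randomization and Blinding adds: "The participants will be randomized into 1:1:1:1 blocks using the random number generator".
- **Role of the same variables in the primary analysis** (Proposed Analysis). The ADAS-Cog score is the dependent variable, and the treatment condition ("active or placebo tDCS; active or placebo cognitive intervention) will be examined as a between-groups variable") is on the explanatory side.
- **Timing of the covariates** (Stepwise Procedures). The screening part of the pre-treatment measurement includes a "health questionnaire (including questions about disease duration, comorbidities and use of medication"). Age and gender are fixed before treatment.
- **Response** (Stepwise Procedures): "we consider the difference of at least three points in the ADAS-Cog and in the pre- and post-treatment measures to be clinical improvement". Participants who meet this are counted as responders.

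**The concern.** A regression that looks for predictors of response needs response as its dependent variable. Here both sides of the model are named and response is on neither. The two outcomes given are treatment assignments, which were set by a random number generator and so cannot depend on a patient's age, gender, comorbidities or medication except by chance.

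Two things are at stake. First, the analysis cannot meet its stated aim: a characteristic that strongly predicts improvement leaves no trace in a model without improvement in it. Second, a coefficient that reaches p < 0.05 because the arms happened to differ at baseline would come from an analysis labelled as finding predictors of response, and could be reported as one.

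**Working it through.** The plan gives no figure for this analysis, so there is none to reproduce. The check is a logical argument, confirmed by simulation.

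**Step 1: what the written model estimates.** Let T = 1 for active tDCS and 0 for sham, let X be the baseline covariates and let Y be ADAS-Cog improvement. Allocation is 1:1:1:1, so two of the four groups receive active tDCS and P(T = 1) = 2/4 = 0.5. Because allocation is random, P(T = 1 | X) = 0.5 for every X. The true slope of T on each covariate is therefore zero. Y does not enter, so no relation between X and Y, or between X, T and Y, can change the result. The same holds for cognitive intervention, and for one joint model or two separate ones.

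**Step 2: what that amounts to.** It compares baseline characteristics between randomised arms. Proposed Analysis already plans this, by ANOVA for continuous variables and chi-square for categorical ones.

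**Step 3: simulation.**

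Inputs from the article: 100 patients, 25 per group (Sample Size); alpha 0.05 (Proposed Analysis); an ADAS-Cog improvement of 3.76 points with SD 1.32 (Sample Size), used only for scale.

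Assumptions, because the article gives no values: tests are two-sided; there is one standard normal covariate X1 and three binary ones, with one coefficient each; cognitive intervention has no effect; X1 shifts improvement by b points per SD, with b = 0, 0.66 or 1.32; the X1-by-tDCS interaction d is 0 or 1.32 points per SD.

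Generating model: Y = 3.76·T + b·X1 + d·X1·T + 1.32·e, with e standard normal. There were 4,000 simulated trials per scenario, analysed with linear models.

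Share of trials with p < 0.05 for X1, or for the interaction in the last column:

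| b | d | As written: tDCS as outcome | As written: cognitive intervention as outcome | Y as outcome: X1 | Y as outcome: X1-by-tDCS |
|---|---|---|---|---|---|
| 0 | 0 | 4.6% | 5.0% | 5.1% | 4.8% |
| 0.66 | 0 | 5.0% | 5.3% | 99.7% | 5.1% |
| 1.32 | 0 | 5.3% | 5.6% | 100% | 4.9% |
| 0 | 1.32 | 5.0% | 5.1% | 98.1% | 99.7% |
| 1.32 | 1.32 | 5.1% | 4.6% | 100% | 99.7% |

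The Y models include the four covariates and both treatments; the last column adds the interaction term. The overall F test of all four covariates with tDCS as outcome rejected in 4.5% to 5.2% of trials.

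**Step 4: simulation error.** At a true rate of 5%, the standard error is √(0.05 × 0.95 / 4000) = 0.0034, so 95% of results should lie within about 4.3% to 5.7%. Every as-written result does.

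The high detection rates in the last two columns depend on the assumed effects. The flat 5% does not: it follows from Step 1.

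**The case against.** **It is probably a slip.** The aim sentence fixes the intent, and the next one reads naturally as shorthand for response to tDCS and response to cognitive intervention. The primary analysis puts treatment on the correct side, so the authors know where it belongs. This is plausible, and it bears on severity. It does not remove the point: the sentence names the outcomes explicitly, nothing else in the article corrects it, and the shorthand reading still leaves the response variable unnamed.

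**An analysis plan would settle the model.** That would answer an omission. Here the article states a dependent variable, and it is the wrong one for the stated aim.

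**The Cox model already examines predictors.** It concerns relapse during follow-up, not response to the 8-week treatment.

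**No design of this kind could be uninformative in every case.** A reader might infer that regressing treatment on covariates can never say anything about response. That is too strong. Restricted to responders, such a regression can carry information on treatment-by-covariate interaction. The article states no such restriction; its intention-to-treat rule is that "all participants will be included in the analysis, including those who drop out before completing the treatment". The conclusion therefore holds for all randomised participants and is limited to them.

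**A 34% false-positive rate.** A reader might multiply four predictors by two outcomes and infer a chance of 1 − 0.95^8 = 0.34 of at least one spurious predictor. The article does not support that figure. It gives no coding for comorbidities or medication, so eight coefficients is a guess, and independence is a further assumption. It is also ordinary multiplicity: eight covariate-by-treatment interactions in a correct model would carry the same 34% under the null. It does not measure this defect and is not relied on here.

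**Conclusion.** The point holds for the text as written. The regression has no response measure, treats randomised assignment as the outcome, and gives the treatments the opposite role from the one they have in the primary analysis. Applied to all randomised participants, it rejects at about 5% whatever the true predictors are, and a significant coefficient reflects chance baseline imbalance. This rests on random allocation and on covariates measured before treatment, both of which the article states.

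Severity is moderate. A reader might infer that the trial's main results are compromised; they are not. This is a secondary predictor analysis. The split-plot ANOVA of ADAS-Cog and the Kaplan-Meier and Cox follow-up analyses do not depend on it.

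**What to change.** Rewrite the sentence that specifies the model:

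- **Dependent variable:** ADAS-Cog change from baseline to post-treatment (week 8), or responder status as defined in Stepwise Procedures. If responder status is chosen, first reconcile that definition (at least three points) with the follow-up paragraph of Proposed Analysis, which cites 3.76 points as the cutoff for improvement. The continuous change does not depend on this.
- **Explanatory variables:** tDCS, cognitive intervention, age, gender, comorbidities and medication use.
- **Only if predictors of differential response to treatment are wanted:** add treatment-by-covariate terms and label them exploratory. Without them, the model identifies predictors of improvement in general.

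The cost is a sentence or two of wording. The ADAS-Cog scores and the covariates are already to be collected, so no new data or patients are needed.

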## Stepwise Procedures

Figure 2 shows the stages of NeuroAD.

**Figure 2 F2:**
[figure not shown]
Flowchart of phases I (double-blind factorial clinical trial), II (crossover) and III (follow-up) of the Neurostimulation combined with Cognitive Intervention in Alzheimer’s disease (AD) Study (NeuroAD). T0: Baseline, pre-intervention measurement. T1–T8: intervention, tDCS and cognitive treatment. T9: endpoint, post-intervention measurement.

The phase I is a double-blind, randomized, factorial clinical trial in which tDCS will be applied in parallel to cognitive intervention in AD patients. This stage includes two measurement time points: baseline (week 0) and post-treatment (week 8). The data collection sessions will be performed by treatment-blinded investigators including the primary and secondary outcomes assessments. The pre-measurement consists of a screening and measurement part. The screening part contains data of the DSM-IV-TR, NINCDS-ADRDA criteria, CDR, MMSE and health questionnaire (including questions about disease duration, comorbidities and use of medication). Adverse effects will be assessed at each session, wherein the tDCS rater will ask the patients whether they feel any discomfort or pain and whether this could be related to tDCS.

Phase II is an open-label, crossover phase in which non-responders from groups (2) and (4) (i.e., those receiving sham tDCS) receive a course of active tDCS using the same parameters and montage of phase I, that is, a direct current of 2 mA (current density = 0.13 mA/cm^2^) for 30 min/day for 24 days, in respective six brain regions.

Phase III is the longitudinal study of NeuroAD in which all active-tDCS responders—that is, responders from groups (1) and (3) from phase I and responders from phase II will be enrolled in a bi-monthly 1-year follow-up. Thus, two months after the last session, the participants will receive ten consecutive tDCS sessions (from Monday to Friday), which will be repeated every other month, until completing a one-year period (totaling 70 follow-up sessions). The tDCS parameters will be the same as those applied during the period between baseline and post-treatment, and the same cortical areas will be stimulated.

The expected significant improvement is reaching 3.76 points in the mean ADAS-Cog, with a SD of 1.32 points, according to Rabey et al. (2013). Thus, we consider the difference of at least three points in the ADAS-Cog and in the pre- and post-treatment measures to be clinical improvement. All participants with clinical improvement will be considered as respondents.

In all steps, the primary and secondary outcomes assessments will be repeated. The pre-intervention measurement is planned to be performed in the week before the intervention starts and the post-intervention measurement is planned for the first week after the intervention.

## Anticipated Results

Considering there is a serious lack of factorial designs for clinical trials in non-invasive cerebral stimulation for AD patients, we aim to ameliorate that situation by observing the effect size and clinical effectiveness of each procedure, not only comparing this intervention against a sham (which could prove the efficacy, but not the clinical effectiveness), but also against a cognitive intervention. Further, we hope to broaden the treatment scope, promoting improvement in cognitive and functional aspects by stimulating different cortical regions, in addition to memory. Therefore, our study may generate key results for clinical practice and patient management throughout the disease.

Then, to the best of our knowledge, our study may be the first to apply a factorial design in non-invasive cerebral stimulation for AD patients, and not only comparing this intervention against a sham (which could prove the efficacy, but not the clinical effectiveness), but also against a cognitive intervention. Next, this factorial design will be able to observe the effect size and clinical effectiveness of each procedure, and will also be able to elucidate whether it would actually be feasible to apply the therapies alone or in combination. Further, we hope to broaden the treatment scope, promoting improvement in cognitive and functional aspects by stimulating different cortical regions, in addition to memory. Therefore, our study may generate key results for clinical practice and patient management throughout the disease.

An additional relevant issue is the longer-lasting effects. Evidence shows that multisession protocols promote neural plasticity and after-effects in AD and other conditions (Fregni et al., 2015; Bystad et al., 2016b). Although a case study that evaluated the effects of tDCS up to 8 months has been reported in the literature (Bystad et al., 2017), we hope to find that bimonthly stimulation sessions amplify the produced effects. Likewise, the use of long-term physiological markers will allow us to know what kind of non-pharmacological therapies produce greater neuroplasticity effects in AD patients, which are responsible for reaching and maintaining better long-term overall performance. The implementation of more effective procedures of plasticity induction in clinical settings is essential—in fact, as a maintenance treatment for bimonthly sessions, tDCS can offer the advantage of a cost-effective approach (reducing missed visits) and a less expensive alternative compared to daily sessions in the long-term. In this way, our findings may also help improve the recommendation management of AD.

Fundamentally, our study presents some methodological limitations that should be discussed, including adherence. The participants must come to our laboratory to receive 24 sessions three times a week. This may result in absences due to transportation problems or personal difficulties. However, different strategies will be adopted to minimize these problems, such as flexible hours and frequent phone calls, encouraging and reinforcing the importance of treatment. Also, we will set a limit of missed appointments so that the treatment process is less rigid, and the patient can resume the missed sessions without compromising the treatment follow-up if necessary. Second, applying the neuropsychological tests could elicit a learning effect. The practice-adjusted RCI of the different cognitive tests used in the clinical trial will be used to minimize this limitation (Goldberg et al., 2015), as described in the statistical analysis. Although some tests may have increased susceptibility to practice effects (Calamia et al., 2012), patients with AD show no significant effects in practice regarding repeated administrations of different cognitive tests after a test-retest interval (Cooper et al., 2004; Foley et al., 2015). A third consideration is the inclusion of only mild AD patients, thereby limiting the generalization to other phases of the disease. Considering cognitive and functional differences between the different stages of AD, we chose to evaluate patients at only one stage of the disease for improved data control. However, this does not preclude future studies comparing patients at different stages of the disease to specifically clarify the best dosage, procedure and number of tDCS sessions and cognitive intervention, considering the clinical symptoms and disease progression of the patients. Finally, although our proposition is to stimulate different regions affected by AD, we cannot assure that there will be no cumulative effects between them. In view of intersubject and intrasubject variations, many studies claim to have the focal power on tDCS, so we cannot rule out the possibility of effect propagation from one region to another (Boros et al., 2008; Cunningham et al., 2015). As our study does not aim to evaluate or compare the efficacy of tDCS at each site separately, cumulative effects from synaptic connections between the involved regions may result in improved cognitive and functional performance, and not cause harm to patients. Nevertheless, it is important to emphasize that we will use several strategies to control bias, such as reduced electrode size, use of neuronavigation to localize target regions in each patient, and the use of standardized coordinates from previous studies for localizing target regions.

In general, we hope that our results can elucidate the relevance of such potential limitations. Additionally, we consider that the current protocol together with our results will have important implications for AD treatment, both theoretically in providing support for new trials and for clinical management, thus providing evidence applicable to the routine care of these patients.
